# Comparing Smartphone Virtual Reality Exposure Preparation to Care as Usual in Children Aged 6 to 14 Years Undergoing Magnetic Resonance Imaging: Protocol for a Multicenter, Observer-Blinded, Randomized Controlled Trial

**DOI:** 10.2196/41080

**Published:** 2023-01-24

**Keywords:** virtual reality, VR, children, anxiety, magnetic resonance imaging, MRI, MRI scans, imaging, randomized controlled trial, MRI preparation, smartphone virtual reality, smartphone intervention, procedural anxiety, psychosocial intervention

## Abstract

**Background:**

A magnetic resonance imaging (MRI) procedure can cause preprocedural and periprocedural anxiety in children. Psychosocial interventions are used to prepare children for the procedure to alleviate anxiety, but these interventions are time-consuming and costly, limiting their clinical use. Virtual reality (VR) is a promising way to overcome these limitations in the preparation of children before an MRI scan.

**Objective:**

The objective of this study is (1) to develop a VR smartphone intervention to prepare children at home for an MRI procedure; and (2) to examine the effect of the VR intervention in a randomized controlled trial, in which the VR intervention will be compared to care as usual (CAU). CAU involves an information letter about an MRI examination. The primary outcome is the child’s procedural anxiety during the MRI procedure. Secondary outcomes include preprocedural anxiety and parental anxiety. We hypothesize that the VR preparation will result in a higher reduction of the periprocedural anxiety of both parents and children as compared to CAU.

**Methods:**

The VR intervention provides a highly realistic and child-friendly representation of an MRI environment. In this randomized controlled trial, 128 children (aged 6 to 14 years) undergoing an MRI scan will be randomly allocated to the VR intervention or CAU. Children in the VR intervention will receive a log-in code for the VR app and are sent cardboard VR glasses.

**Results:**

The VR smartphone preparation app was developed in 2020. The recruitment of participants is expected to be completed in December 2022. Data will be analyzed, and scientific papers will be submitted for publication in 2023.

**Conclusions:**

The VR smartphone app is expected to significantly reduce pre- and periprocedural anxiety in pediatric patients undergoing an MRI scan. The VR app offers a realistic and child-friendly experience that can contribute to modern care. A smartphone version of the VR app has the advantage that children, and potentially their parents, can get habituated to the VR environment and noises in their own home environment and can do this VR MRI preparation as often and as long as needed.

**Trial Registration:**

ISRCTN Registry ISRCTN20976625; https://www.isrctn.com/ISRCTN20976625

**International Registered Report Identifier (IRRID):**

DERR1-10.2196/41080

## Introduction

Magnetic Resonance Imaging (MRI) is a commonly used imaging technique that provides detailed images without the use of ionizing radiation. Research has shown that pediatric patients can experience a range of negative emotions during this procedure [1]. There are several components within an MRI procedure that can induce anxiety such as the loud noises generated during an MRI scan and the prolonged time spent in a confined space [2]. Although there is little research on how children experience an MRI scan, one study found that about 50% of children between aged 5 to 12 years with nonacute medical conditions experienced anxiety and discomfort during an MRI scan [3]. Younger children can be overwhelmed by the MRI environment with noises they have never heard before and by the MRI machine, whereas older children can experience claustrophobic feelings [4]. This can result in poor cooperation, eg, following breathing instructions or excessive movements, which has a negative effect on the scan quality since up to 90% of the MRI artifacts can be attributed to movement [5]. To combat MRI-related anxiety and discomfort, children are often sedated or completely anesthetized up to the age of 6 years [6,7]. The use of general anesthesia is not without risks. Pediatric patients can experience side effects such as emerging delirium, respiratory depression, nausea, vomiting, agitation, and cardiovascular bradycardia [8-11]. Different methods have been implemented to reduce the need for anesthesia and pre- and periprocedural anxiety, such as behavioral rehearsal using mock MRI scans [12], play therapy [13], and distraction during the procedure using MRI-compatible audiovisual tools [14]. The use of these interventions has been found to be effective but are time-consuming and often rely on the guidance by a professional [2].

To alleviate MRI-related anxiety, virtual reality (VR) offers a promising alternative to prepare children for the procedure. VR is a way to experience computer-generated scenarios that can be used to create experiences similar to or completely different from reality. With audiovisual stimulation, the user can interact with the virtual environment [15]. Research has shown that VR can positively affect self-reported pain and anxiety during several medical procedures [16]. Most VR studies focused on distracting patients during a medical procedure. Exposure, however, is one of the most effective interventions to reduce anxiety, and only a few studies investigated the impact of VR exposure before a medical procedure [17-20].

To our knowledge, there has been little research into the effectiveness of VR as preparation for an MRI in a clinical setting. In a cross-sectional study of 23 pediatric patients by Ashmore and colleagues [21], the VR preparation was highly rated on enjoyment, helpfulness, and ease of use. They also showed that for some pediatric patients, VR preparation helped them to undergo an MRI scan without general sedation. In an exploratory study, Nakarada-Kordic and colleagues [22] compared the feeling of being inside an MRI scanner in VR versus being in a mock MRI scanner in a sample of 20 adult participants. The authors did not find a significant difference between the experience of VR MRI and mock MRI scans, and 86% of the participants reported that the VR simulation could be a helpful way to prepare for a real MRI exam. Stunden and colleagues [19] studied VR exposure based on a 360-degree movie versus a standard preparatory manual and a hospital-based Child Life Program on anxiety in a simulated MRI scan in 92 children aged 4-13 years but could not demonstrate a difference between the 3 groups. While this study failed to find a significant effect of VR exposure on procedural anxiety, it did have several drawbacks. They used a simulated MRI scan instead of an actual clinical MRI scan to test intervention effectivity. This may have limited the emotional response generated. Finally, the use of 360-degree recorded images instead of rendered 3D graphics may have limited immersion, which could be an important mediator of intervention effectivity as shown in VR-based pain distraction [23].

VR preparation of pediatric patients for medical procedures is often done with a head-mounted displays tethered to a powerful computer within the hospital setting. A disadvantage of this approach is that it requires a trained professional to do the VR preparation and that the time a child can be prepared is often limited. An alternative is to deploy the VR preparation to a smartphone, head-mounted by means of a Google cardboard. With a smartphone VR app, children can get prepared in their own home environment under parental supervision at their own pace and as often and as long as they need. Another advantage of a smartphone VR app is that it can be employed on a large scale and requires limited involvement of health professionals, ultimately saving costs associated with the traditional VR goggles tethered to a powerful computer. Moreover, costs associated with a Google cardboard are negligible compared with computer-tethered or dedicated head-mounted VR displays.

The objective of this study is (1) to develop a realistic VR smartphone app to prepare children for an MRI scan, using an immersive, interactive VR approach with a fully rendered environment; and (2) to present a methodological approach to conduct a randomized controlled trial (RCT) that can test the effectiveness of the VR intervention in children who need to undergo an MRI scan. The clinical effect of the VR smartphone app will be compared with routine clinical care (care as usual [CAU]). The primary outcome is periprocedural anxiety. Secondary outcomes include preprocedural anxiety, user experience, child behavioral and emotional problems, and parental anxiety. We hypothesize that the VR preparation will result in a larger reduction of the periprocedural anxiety of both parents and children as compared to CAU. We further hypothesize that VR preparation will lead to a larger reduction in parental anxiety and preprocedural child anxiety as compared to CAU.

## Methods

### VR Design

The VR tool encompasses a highly realistic virtual environment that replicates the MRI experience of the Erasmus University Medical Center (MC)–Sophia Children’s Hospital, Rotterdam, the Netherlands. The designed virtual MRI environment does not significantly differ from that of the Amsterdam University Medical Centers (UMC).

A multidisciplinary team, consisting of child-life specialists, child psychologists, a child psychiatrist, anesthesiologists, a 3D-acting director, and a 3D project manager designed the script of the VR experience. Working together with specialized VR developers and animators, multiple 3D characters, asset, and environment artists created the scenery and character modeling. During the design and development phases, team meetings were held to review the process and make any necessary adjustments. Overall, the main goal was to create a dynamic and interactive environment that will prepare children for the MRI procedure in a realistic and child-friendly manner. Once the VR software was created, it was pilot-tested in healthy children (n=10). Based on the observations and responses of the pilot test, final adjustments were made.

### Technical Specifications

#### Software and Hardware Details

The 3D software in the VR smartphone app was developed using the Unity games engine, a cross-platform game engine developed by Unity Technologies. The app is designed to be used in a Google cardboard–like VR goggle, meaning a VR goggle relying on the use of a smartphone for its VR capabilities. The cardboard includes adjustable lenses and head straps—this makes the cardboard suitable for children. The software is usable on iPhone 5s or above or Android smartphones with operating system 4.4 or above. Participants can download the app in the Apple App Store or Google Play Store.

#### VR Storyline

The duration of the VR MRI smartphone intervention is approximately 5 minutes. The VR app takes place in a typical MRI room as seen in Figure 1 (and Multimedia Appendix 1), with an explanation given to a child by MRI technicians depicted on a monitor in the virtual MRI room. This design has been chosen to maximize the ease of program portability between different hospital settings and even between different languages by making it easy to switch out the supporting video with a localized alternative.

Participant can choose between 2 versions: one version for an upper body MRI and another version for a lower body MRI. The MRI experience starts with a technician that is visible on a screen on the wall of the MRI room. The technician introduces herself and explains that the participant is in the MRI room, what an MRI scan is, and that it makes a lot of noise but is not painful. She also explains that no metals are allowed in the MRI environment and that participants are not allowed to wear jewelry during the actual MRI examination. After this initial explanation, the participant is allowed to move around the virtual MRI room. The MRI room and machines are visible in 360 degrees and can be seen if the participant moves with his head. The participant can move around the MRI machine by looking at marked focus points (feet symbol) on the floor of the MRI room. When the participant is located behind the MRI machine, the technician explains that the MRI bore is open from the front to the back. When the participant is back at the starting position in the front of the MRI machine, the technician explains that some children like their parents to be present during the MRI, that they will get earplugs because of the MRI noise, and that it is important that they lie still within the MRI machine. After that, the participant can look at a focus point on the ceiling above the table of the MRI machine and is then transferred to this location. Subsequently, the participant is slowly transferred within the bore of the MRI machine. Depending on the version of the MRI machine, the participant is transferred within the bore of the MRI machine headfirst (upper body MRI) or feetfirst (lower body MRI). A scan with the duration of 1 minute is performed accompanied by varying MRI noises. When the scan is completed, the VR experience is finished, and the app returns to the home screen.

**Figure 1 figure1:**
[figure not shown]
Image of the 3D environment in which the virtual reality experience takes place.

### Study Design

This multicenter, single-blinded, RCT is being performed at the Erasmus MC–Sophia by the Departments of Child and Adolescent Psychiatry/Psychology, Radiology, and Pediatric Anesthesiology and at the Amsterdam UMC–Emma Children’s Hospital by the Department of Radiology. Children (N=128) will be randomly allocated to 2 parallel groups: VR smartphone application (n=64) or CAU (n=64). CAU involves an information letter given to the parents that consists of information about the MRI examination, the screening questionnaire that is used, and how to best explain the MRI exam to their child. Randomization will be performed as block randomization with a 1:1 allocation.

### Ethics Approval

The study was approved by the medical ethical committees of the Erasmus MC (NL68075.078.19) and Amsterdam UMC (MEC-2019-0242).

### Inclusion and Exclusion Criteria

Eligible participants are children aged between 6 and 14 years undergoing an MRI scan at the Erasmus MC–Sophia Children’s Hospital or the Amsterdam UMC–Emma Children’s Hospital (2 specialized children’s university hospitals in the Netherlands) in the period between May 2021 and December 2022. Children that meet the following criteria will be excluded from participating: any intellectual disability, inability of parents to read or write in the Dutch language, epilepsy, visual impairments, and the need of general anesthesia during the scan.

### Sample Size

To conduct analysis of covariance (ANCOVA) on the level of periprocedural anxiety at time point (T) 3 (primary outcome) with a Cohen *d* of 0.5, an α of .05 (2-tailed), and a power of .80, a sample size of 128 patients is needed (64 patients per group). Based on earlier studies, we anticipate finding a medium effect size [16].

### Randomization

Participants will be randomly allocated to the intervention (VR) or control group (CAU) with a 1:1 allocation. A computer-generated randomization schedule will be used, stratified by age group (aged 6-10 vs 10-14 years) and the type of MRI (upper body vs lower body).

### Patient Recruitment and Procedure

For the prospective recruitment of patients, in concert with the radiologist, the planned MRIs will be scanned a month ahead for eligible patients. They will be informed about the study by mail or phone. If needed, they will be reminded by phone in the following weeks. Besides the reminder, this will help to overcome doubts, because the staff can answer questions or motivate the patients to participate.

All participants will receive an invitation, information folders, and an informed consent form. Participation is not obligatory, and all data will be anonymized. Parents of all the patients will be asked to sign informed consent. Children aged 12-14 years will also be asked to provide informed assent themselves. Patients aged younger than 12 years will give their verbal permission.

After receiving signed informed consent, the participants will be stratified by the type of MRI scan (head or body scan). Then, they will be randomly assigned to the VR group (n=64) or the CAU group (n=64).

The children assigned to the VR group will receive Google cardboard–like VR glasses and instructions on how to download the VR app on their phone and use the VR intervention at home. They will receive a log-in code to use the smartphone VR app. Adherence will be promoted by giving the participants detailed information about the purpose of the study and how to use the VR preparation app and explaining how they can get help from the contact support staff if there are difficulties with the app or VR glasses.

The allocation sequence was executed by a researcher who is not involved in the assessment phase. The psychologist who assesses the child’s anxiety state is blinded to the group assignment. This way, blinding for the treatment allocation will be guaranteed. Parents and children in both groups will be asked not to discuss their treatment allocation with the nurse, radiologist, or research psychologist.

Questionnaires will be assessed at the following time points: (1) T1, the weeks before the MRI scan (at home); (2) T2, the day of the MRI scan, before the procedure will start (in the waiting room); and (3) T3, right after the MRI scan (in the waiting room). The T3 questionnaires will retrospectively assess the child’s experience during the MRI scan. In this way, we can measure the anxiety during the MRI scan without the interruption of the procedure.

The children assigned to the CAU group will receive an information letter in which child-friendly information is provided about the VR examination.

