### Outcome Measures

The study design and variables at each time point are presented in Figure 2. The primary outcome is periprocedural anxiety at T3 (State-Trait Anxiety Inventory for Children [STAI-C] and Visual Analog Scale [VAS]). Secondary outcomes include preprocedural anxiety (VAS and STAI-C), user experience, child behavioral and emotional problems (Child Behavioral Checklist [CBCL]), and parental anxiety (State-Trait Anxiety Inventory [STAI]).

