#### Child Anxiety

The anxiety level of participants is measured before and after the MRI scan (T2 and T3) with the STAI-C, a questionnaire where parents and children evaluate statements on a scale from 0 (not at all) to 4 (completely true). The STAI-C is a widely used and validated self-report instrument for measuring state and trait anxiety [24]. The STAI-C has a good-to-excellent interobserver and intraobserver reliability and was validated in Dutch [25]. The VAS will be used to assess the child’s anxiety level by the child himself, the parents, and the medical staff. The VAS shows 6 faces in order from not scared at all (most left face) to extremely scared (most right face; see Figure 3) [26]. The participants select the expression that fits their feeling before and after the MRI scan (T2 and T3). Because of the nonverbal character and the simplicity, this instrument offers a quick and reliable assessment that can be used in different settings [27,28]. The VAS is a widely used and studied instrument, has been shown to have a good reliability and validity, and is validated in Dutch [29]. The medical staff who accompanied the child were instructed to observe the anxiety of the child before the procedure in the MRI room and during the MRI scan (T2 and T3) by using the VAS [30].

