#### Primary Study Parameter(s)

To test the efficacy of the VR intervention, we will compare the VR group to the CAU group with an ANCOVA. The primary outcome variable is the child’s situational anxiety during MRI scan (T3; VAS child, continuous score), corrected for age, sex, baseline anxiety, and CBCL scores as well as type of MRI. In case of nonnormality, we will perform a Mann-Whitney *U* test.

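### The blinding guarantee does not reach the primary outcome, which the unblinded child reports, and the one rating from outside the family is named in no analysis

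*Protocol article*

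**What the plan says.** The title calls the trial observer-blinded, and Study Design calls it single-blinded. Patient Recruitment and Procedure gives the basis: "The psychologist who assesses the child’s anxiety state is blinded to the group assignment". The next sentence draws the conclusion: "This way, blinding for the treatment allocation will be guaranteed". The section then adds: "Parents and children in both groups will be asked not to discuss their treatment allocation with the nurse, radiologist, or research psychologist".

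The same section describes what one arm receives: "The children assigned to the VR group will receive Google cardboard–like VR glasses and instructions on how to download the VR app". The comparator is an information letter.

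Primary Study Parameter(s) fixes the variable and its rater: "The primary outcome variable is the child’s situational anxiety during MRI scan (T3; VAS child, continuous score". Outcome Measures also lists the STAI-C under the primary outcome and names no rater. Child Anxiety says that parents and children complete the STAI-C, and that the child, the parents and medical staff give the VAS. On the staff rating it says: "The medical staff who accompanied the child were instructed to observe the anxiety of the child". That rating is made at T2 and T3.

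**The concern.** A blinded assessor protects an outcome only if the assessor produces the rating. Here the guarantee rests on a psychologist to whom no scale is attributed, while the primary rating comes from the person who used, or did not use, the VR app. Families are told in detail about the purpose of the study, and the child picks one of six faces after the scan, looking back on it. These conditions leave room for a child to report what seems hoped for. A difference in child VAS could then reflect a real reduction in anxiety, a difference in reporting, or both.

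The trial collects one anxiety rating of the child from outside the family, but the statistical section does not say what will be done with it. Strengths and Limitations discusses how VR use is measured, attention, phone differences and generalizability. It does not mention unblinded self-report. A report that carried the guarantee and the title's label forward would overstate the protection of the primary result.

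**Working it through.** **Step 1: who rates what, and does that person know the arm?** (Outcome Measures and its subsections; Patient Recruitment and Procedure; Statistical Analysis)

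| Rating | Rater | Knows the arm? | Named in an analysis? |
|---|---|---|---|
| VAS, child, T3 | Child | Yes: glasses and app, or a letter | Yes, primary |
| VAS, child, T2 | Child | Yes | Yes, by the identical analysis for preprocedural anxiety |
| STAI-C, T2 and T3 | Child and parents | Yes | Under the primary outcome in Outcome Measures; not in Primary Study Parameter(s) |
| VAS, parent, T2 and T3 | Parents | Yes | Not by name |
| STAI, parents' own anxiety, T2 and T3 | Parents | Yes | Yes: parental anxiety, repeated-measures ANCOVA |
| VAS, staff, T2 and T3 | Medical staff with the child | Not stated | Not by name |
| Any scale rated by a psychologist | None listed | Stated to be blinded | None listed |

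The request that families not disclose their allocation itself presumes that they know it. The one person stated to be blinded has no listed rating. Whether the primary outcome is the child VAS alone or the child VAS with the STAI-C, its raters know the arm. The exploratory regressions refer only to child anxiety and name no rater.

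**Step 2: reproduce the planned sample size.** Inputs from Sample Size: d = 0.5, two-sided α = .05, power .80.
- Normal approximation: n per arm = 2(1.960 + 0.842)²/0.5² = 62.8, so 63.
- Two-sample t-test: 63.77, so 64 per arm and 128 in total, with power 0.801.

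The stated 128 is reproduced, and nothing in this point changes it.

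**Step 3: how sensitive is the primary test to a reporting shift?** The documents give no size for such a shift, so b is an assumption shown over a range. Suppose that there is no true effect and that knowing the allocation shifts VR children's self-report by b SD. With 64 per arm and no covariates:
- standard error of the difference in SD units = √(2/64) = 0.1768
- noncentrality = b/0.1768, with 126 degrees of freedom
- smallest observed difference with p<.05 = 1.979 × 0.1768 = 0.35 SD

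| Assumed b (SD) | Share of d = 0.5 | Noncentrality | Chance of p<.05 |
|---|---|---|---|
| 0 | 0% | 0 | 5% |
| 0.1 | 20% | 0.566 | 8.7% |
| 0.2 | 40% | 1.131 | 20.2% |
| 0.3 | 60% | 1.697 | 39.1% |

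If the ANCOVA covariates reduce residual variance, the same raw shift would reach significance more often than shown.

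**The case against.** The strongest reply is that the article never claims to blind the child. Its labels are observer-blinded and single-blinded, it treats families as aware of their arm, and the guarantee follows directly after the sentence about the psychologist. Unblinded self-report is hard to avoid when VR glasses are compared with a letter, and it is a legitimate primary endpoint. All of this stands. A reader might infer that the article asserts a blinded child, and it does not. What remains is that a guarantee attached to a person with no listed rating does not cover the primary variable.

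A blinded psychologist who administers the faces scale could still limit prompting. That is possible, but the article does not say who administers it, and the rating would still be the child's.

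A reader might also infer that the staff VAS has been left out of every analysis. The text does not establish this. Outcome Measures lists the VAS without a rater, the secondary section covers only the main secondary outcomes, multiple informants are counted as a strength, and an analysis plan that is not shown could include it. The supportable statement is that the staff VAS is named in no analysis in the article. Such a plan would not repair the blinding statement.

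Nor can the staff be taken as blinded. Families are asked not to tell the nurse, radiologist or research psychologist, and the article does not make clear that these are the staff who rate.

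Finally, the calculation would apply to any trial of this size with an unblinded self-reported outcome. That is correct. It shows sensitivity, not that bias of any given size exists here.

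**Conclusion.** The point holds. The article presents blinding as guaranteed on the strength of a blinded psychologist, yet it attributes no outcome to that person, and the primary variable is reported by a child who knows the allocation. This contradiction lies in the text itself, so no further document can remove it. The observer-blinded label does not protect the primary result from expectancy or wish-to-please reporting.

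The size of any such bias is unknown. Under the assumed shifts of 0.1 to 0.3 SD, with no true effect, 64 per arm and no covariates, the chance of a significant primary result rises from 5% to between about 9% and 39%. This does not show that the primary endpoint is invalid or should be replaced. It shows that the blinding claim needs narrowing and that the one non-family rating deserves a stated place in the analysis.

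**What to change.** 1. Replace the guarantee with a statement that the primary outcome is self-reported by children who know their allocation, and that blinding applies only to the psychologist.
2. State what the psychologist rates or administers.
3. State whether the staff who give the VAS are blinded, and whether they are the people families are asked not to tell.
4. Before analysis, prespecify staff-rated VAS at T3, which is already part of data collection, as a supportive secondary outcome with the same ANCOVA as the child VAS. Report the two side by side. Observed and felt anxiety can differ, so disagreement alone does not prove reporting bias. How much weight agreement carries depends on the answer to item 3.

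The cost is a change of wording, one more model on data already in the design, and a less favourable blinding claim. Sample size, recruitment and the primary endpoint stay as they are. A tick-box for the staff's guess of the allocation is optional, could serve only children still to be scanned, and is not needed for the fix.
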